### Process evaluation

The aim of the process evaluation is to test the intermediate processes outlined in the WELLFOCUS model between the intervention (tested by fidelity assessment) and outcome. Process evaluation strategies include ratings and notes taken by the co-facilitators directly after each session and phone call for each participant and each week, and additional qualitative interviews and focus groups after the end of the therapy.

The co-facilitator collected process evaluation includes five assessment strategies at treatment receipt and skills enactment level which map onto the WELLFOCUS intervention model:

1. Presence of participants in group sessions

2. Engagement of participants in exercises during treatment groups and a facilitator rating of whether this was perceived as beneficial

3. Facilitator rating of behavioural intent to undertake the ‘ongoing exercise’, based on the session in which the ‘ongoing exercise’ was set

4. Facilitator rating of engagement and benefit from the ‘ongoing exercise’, based on the session in which the ‘ongoing exercise’ was reviewed

5. Length and content of the weekly telephone calls.

Qualitative process evaluation comprises individual interviews and focus groups with trial participants, and individual interviews with group facilitators. Participants will be asked to take part in either an individual interview (50%) or a focus group (50%).

Semi-structured interviews will ask about participants’ experience of taking part in the study, how the intervention was delivered, and what impact the intervention has had on their well-being and life generally. Questions will also relate to the WELLFOCUS model and processes facilitated by the therapy. Suggestions for further improving the intervention and trial processes will be collected. As far as possible, those who dropped out of the intervention arm or attended irregularly will be asked for reasons including contextual factors influencing attendance and for suggestions to improve attendance rates in the definitive RCT. Focus groups will also allow discussion of any suggestions for improvements of the intervention. Hence, topics that come up in interviews, particularly about problematic issues in relation to therapy content, delivery, and study procedures, will feed into focus groups.

All clinicians involved in providing the therapy will be interviewed to obtain feedback on the WELLFOCUS manual, the intervention delivery, and the trial procedures.

### Trial procedures

All researchers are trained in the use of all standardised outcome assessments and in semi-structured interviews or focus groups for the process evaluation. Ongoing supervision is provided from experienced clinical researchers.

### Recruitment and randomisation

The study is introduced to all staff members in the participating teams. Care coordinators, key nurses or other appropriate staff members are asked to identify potentially eligible service users from their case load. Potentially eligible participants receive information about the study from the clinician. In addition, information about the study is sent to eligible service users on two research registers (which involves consent to be contacted by researchers). These are followed-up for recruitment via telephone by the research team. An appointment is scheduled for assenting participants from all sources with a member of the research team to provide further information on the study. In this meeting, the study is explained, written information is provided, and an opportunity is given to ask any questions. If the participant wishes to have time to consider participation, a second meeting is scheduled. Once the participant has given informed consent, baseline assessments are completed. Participants receive an ID number which is entered in the web-based randomisation system together with age (for validation). Some teams may have fewer than 16 eligible participants, and the minimum number of participants will be 8 (i.e., 4 per arm), with block for randomisation. Where possible we will over-recruit to a maximum of 20 participants in other teams. When participants from a participating clinical team have all been entered into the database, randomisation is conducted. Randomisation involves independent allocation to one of the two trial arms on a 1:1 basis. The use of stratification was considered disproportionate for a pilot RCT. The generation and implementation of the randomisation sequence is conducted independently by the King’s Clinical Trials Unit (registration number 053).

### Assessment

Outcomes are measured pre-randomisation and at the end of the intervention (i.e., 3 months after baseline). Every effort will be made to include patients who drop out of treatment in the follow-up assessments to enable intention-to-treat analysis [30]. Process and fidelity measures are collected by the co-facilitators for each participant after each group session. Qualitative process evaluation is conducted with those in the intervention arm, who are asked to participate either in an individual interview or in a focus group (with alternating allocation based on finishing order of groups). Participants are offered £20 as compensation for their time after completing each assessment and either the interview or focus group (i.e., £60 in total for intervention, £40 for control). The £20 difference in payment between the groups might increase follow-up rates for the process evaluation data from intervention group participants, but remuneration for the outcome evaluation is the same for both groups.

### Approaches to minimise bias

It is not possible for service user participants or facilitators to be blind to allocation status. The resources needed to ensure blinding in research assessors would be disproportionate in a pilot study; therefore, this trial is unblinded. However, several approaches will be used to minimise bias.

#### Addressing bias at participant selection

This study uses a convenience sample of service users considered by team leaders to be fit to participate. This may lead to selection bias. However, internal validity is protected due to the random allocation strategy and not revealing the block size.

#### Addressing bias at allocation

All randomisation is undertaken by the independent King’s Clinical Trials Unit.

#### Addressing bias in baseline data

Baseline data are collected before allocation, to reduce assessment bias due to inadequate concealment.

#### Addressing bias in the intervention

Fidelity to the WELLFOCUS manual is monitored to ensure comparability of the intervention between local groups.

#### Addressing bias in follow-up data

All participating services users are followed-up and included in the analysis using an intention-to-treat approach to reduce the impact of selective attrition.

#### Addressing bias in outcome data collection

Bias in the outcome data is minimised by the use of standardised objective assessments and by rater training and supervision. Post-treatment outcomes are, where possible, assessed by researchers who were not involved in the participant’s baseline assessment or their group.

#### Addressing bias in process evaluation

As far as possible the focus group and interview data are collected by a researcher not involved in delivering the intervention to the respective participants, to minimise social desirability bias.

#### Addressing bias in analysis

No data regarding the allocation status are stored in the data entry database, following Good Clinical Practice [61]. The primary data analysis is undertaken blind to allocation status*.* Allocation status is coded as A and B in all data requests.

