## Methods

### Hypotheses

While we shall conduct hypothesis testing, this is not the main objective of the study, as this is the purpose of the future definitive RCT. The reporting of the study will not therefore emphasise the results of hypothesis testing over the reporting of whether the objectives were met [26].Our hypotheses are derived from the WELLFOCUS Model shown in Figure 1. Regarding the effect of the intervention, we hypothesise that participants receiving the intervention will experience, compared to the control group, an improvement in well-being (primary outcome) and good feelings, symptoms, connectedness, hope, self-worth, empowerment, and meaning in life (secondary outcomes).

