#### Objective 3: Piloting the evaluation strategy

The usefulness of fidelity and process evaluation approaches will be determined by exploring whether researcher ratings of fidelity to the manual and process factors, such as engagement and beneficial effect of exercises, helps to improve prediction of outcome and future attendance as compared to recording group attendance only. The confidence interval approach will be used to help determine the suitability of the outcome measures and to inform the sample size calculation for a definitive RCT. This approach involves estimating the confidence interval of the difference between intervention and control group at follow-up, adjusted for baseline. The inclusion of zero (i.e., point of no effect) and the inclusion of a clinically relevant effect into the confidence interval will help to estimate the suitability of measures for a definitive RCT [28]. Further considerations to be taken into account for the choice of outcome measure for the definitive RCT will include the acceptability of the scale (as measured by the number of missing responses), the magnitude of correlation between baseline and follow-up on this scale, and the overall variance of the scale. The group means, standard deviations, and correlations between baseline and follow-up will be used to inform the sample size calculation for the definitive RCT.

In addition, outcomes will be analysed to estimate effectiveness of the intervention. This analysis will be done on an intention-to-treat basis, with participants analysed in the group to which they were randomised irrespective of their compliance with the assigned trial arm. To estimate effectiveness of the intervention, WEMWBS (primary outcome) at pre-treatment (baseline) and 3-month follow-up will be analysed using a random effects regression of outcome on trial arm adjusted for baseline score including a random effect to allow for between group variations in the intervention arm. Where relevant, we will also consider using other approaches to address missing data such as complier-average causal effect approaches [63].

Divergence of normality will be assessed for the distribution of all variables as will linearity of correlations and equality of variance. The choice of statistical methods will be adapted accordingly. *P* values of 0.05 will be considered significant in all cases. All analyses will be carried out in SPSS Version 20 and Stata Version 12.

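### The A/B-coded blind analysis is not achievable as described with a therapy-group effect in the intervention arm only; separately, method choice is tied to raw distributions, not residuals

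*Protocol article*

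**What the plan says.** Under Addressing bias in analysis, the protocol article claims: "The primary data analysis is undertaken blind to allocation status". The means given is: "Allocation status is coded as A and B in all data requests".

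Under Analysis plan, Objective 3, the primary model for the WEMWBS at baseline and 3 months is one in which the scores are "analysed using a random effects regression of outcome on trial arm adjusted for baseline score". To this the article adds a second element, described as "including a random effect to allow for between group variations in the intervention arm". The analysis is by intention to treat, with "participants analysed in the group to which they were randomised irrespective of their compliance with the assigned trial arm".

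The same section then says: "Divergence of normality will be assessed for the distribution of all variables as will linearity of correlations and equality of variance". The next sentence reads: "The choice of statistical methods will be adapted accordingly".

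Two other statements bear on the weight of the point. Approaches to minimise bias says that participants, facilitators and assessors are not blinded. Hypotheses says: "While we shall conduct hypothesis testing, this is not the main objective of the study".

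**The concern.** There are two separate matters.

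**The blind.** Coding arms A and B hides the allocation only if the analysis treats the two codes alike. This model does not, because one arm has a between-group variance and the other has none. A reader who knows that everyone else in the trial is unblinded will give credit to a blinded analysis. The safeguard should therefore work with the model actually named.

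**The choice of method.** The article ties the method to distributional checks on all variables. That is the wrong object to check for this model, and it makes the primary method depend on the data. At stake is the estimated difference with its confidence interval, which Objective 3 uses to judge which outcome measures suit the definitive trial and to inform its sample size.

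**Working it through.** **1. The plan's own figures.** Inputs from Sample size: 80 randomised, 20% drop-out, so 80 × 0.8 / 2 = 32 per arm; significance level 0.05, taken as two-sided. With baseline adjustment, z = ES × √(32/2) / √(1 − r²) and power = Φ(z − 1.96).

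| ES | r | z | Power | Stated |
|---|---|---|---|---|
| 0.5 | 0.7 | 0.5 × 4 / 0.714 = 2.80 | 0.80 | 0.80 |
| 0.5 | 0.6 | 0.5 × 4 / 0.8 = 2.50 | 0.71 | 0.71 |
| 0.6 | 0.6 | 0.6 × 4 / 0.8 = 3.00 | 0.85 | 0.85 |

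All three reproduce. Nothing below alters them.

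**2. Why the codes do not blind this model.** Let T = 1 in the intervention arm. The described model is

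Y = β0 + β1·T + β2·baseline + T·u(group) + e.

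Without T·u(group), exchanging A and B only reverses the sign of β1, so the analyst can fit the model without knowing which code is which. With it, the outcome variance given baseline is σu² + σe² in the intervention arm and σe² in the control arm. Exchanging the codes then gives a different model, and the analyst must be told which code receives u. The data can also give it away: WELLFOCUS groups exist only in the intervention arm (Control group; Intervention group), so a therapy-group identifier filled in for one code alone identifies that code with certainty.

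**3. How far neutral labels alone would go.** Suppose both arms carried a neutral wave-by-arm label, which the article does not describe. In a simulation (20,000 runs, five groups of six per arm), an analyst guessed that the arm with more between-group variation was the intervention.

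| Assumed ICC | Correct guesses |
|---|---|
| 0 | 50% |
| 0.05 | 60% |
| 0.10 | 67% |
| 0.20 | 79% |

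The ICCs are assumptions; the article gives none. Neutral labels help, but a script locked before the data are seen is still needed.

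**4. What the checks should look at.** The model conditions on baseline and arm, so it requires no distribution for either, and arm is binary. Its distributional assumptions are on e and u. A check on all variables can therefore flag a problem the model does not have, such as skewed baseline scores, and can miss one that it does have.

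**5. What an open choice could do.** Simulation under no effect: 32 per arm, 6,000 runs per scenario, normal or log-normal scores, r = 0.6 or 0.7, no clustering. The set of methods is an assumption, since the article names no alternatives.

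| Strategy | Type I error at nominal 0.05 |
|---|---|
| One fixed baseline-adjusted model | 0.046 to 0.053 |
| Fixed rule: rank-based adjusted model if the pooled normality test has p < 0.05 | 0.044 to 0.053 |
| Smaller p of the parametric and rank-based adjusted models | 0.059 to 0.073 |
| Smallest p of five methods | 0.106 to 0.129 |

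The simulation standard error near 0.05 is √(0.05 × 0.95 / 6,000) = 0.003. The first two rows are thus compatible with 0.05. Adapting to the data does no harm here when the rule is fixed; choosing on the result does.

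**6. The two matters do not depend on each other.** Exchanging A and B leaves a two-sided p-value unchanged. Even a perfect A/B blind hides only the direction of the effect, so it would not prevent the inflation in the last two rows.

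**The case against.** The strongest defence is that a blind can be kept with this model. Patients are randomised by clinical team, in waves that contain both arms, so a neutral wave label could be supplied for everyone, or the model could be fitted under both codings. The article does not say that group identifiers go to the analyst for one arm only. Operating details of this kind, like thresholds and named fallback methods, commonly sit in a full protocol or statistical analysis plan that is not shown here.

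Much of this stands. A reader might infer that a blind analysis is impossible; it is not, and the accurate statement is that the article's description does not achieve it. The absence of thresholds and fallbacks is no fault of the article. What remains is what the article does state: a blind resting on A/B codes, a model that treats the codes differently, and a method choice that follows checks on all variables.

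A reader might also infer that A/B coding is the only protection against selective analysis. The article contradicts that. It fixes the primary outcome, the time point, a default model and the intention-to-treat set; it keeps allocation data apart from outcome data; and it says reporting will not put hypothesis tests ahead of the pilot objectives.

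Finally, a reader might infer a fall in power from 0.80 to about 0.50, by supposing that non-normality would lead to an unadjusted rank test. The article names no such test and commits to baseline adjustment for both the effectiveness model and the confidence interval. Several alternatives to the default model would keep baseline, and the usual efficiency figure for the rank test applies to normal data, where no switch would be made.

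**Conclusion.** The point holds at modest severity. The analyst blind is a stated property that the described primary model does not have. This follows from the text and needs no numerical assumption beyond the group effect being confined to the intervention arm, as written. Separately, the stated basis for changing method is misdirected, because it refers to the variables rather than to residuals and random effects.

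No sample size or power figure changes. The type I error range of about 0.06 to 0.13 is illustrative: it assumes a particular set of methods, selection on the p-value and no clustering, and nothing in the article says that such selection is planned. The weight is limited further because this is an openly unblinded pilot aimed mainly at feasibility and estimation.

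**What to change.** 1. **Blinding: choose one.** Either state that the primary script is locked in two versions (group effect in A, group effect in B), both are run, and unblinding selects the one reported; or delete the claim of a blind analysis. For the first option, give both arms a neutral wave label so that either version can run, test the script on scrambled data, and keep attendance and process data, which exist only for the intervention arm, in a separate file until then.
2. **Method.** Keep the baseline-adjusted model with the therapy-group effect as primary whatever the raw distributions. Replace the check on all variables, for this analysis, with a check on its residuals.
3. **Sensitivity analysis.** Name one in advance that retains baseline and group, for example a bootstrap interval that resamples whole therapy groups and individual control patients. With about five groups this is a rough check and should not replace the primary result.

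The cost is a few sentences, minor programming and less freedom for the analyst. Recruitment, assessments and sample size are unaffected.

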### Data handling

All study data will be input by the research workers who collected the data. Rigorous approaches to validating and verifying the data will be used, including rater training to achieve an acceptable concordance in administering standardised assessments, development of a database with allowable values for variables as a validation check, double rating for 10% of the data to identify transcription errors, and data cleaning and preliminary analysis led by a statistician to identify invalid responses, checking for outliers, and unexpected patterns in the relationships between variables.

Protected data storage with clear access protocols in line with Good Clinical Practice Guidelines is used to store allocation and outcome data separately. All data are stored in either a locked filing cabinet or in an electronic password-protected database.

### Analysis plan

All qualitative data will be audio taped, fully transcribed, and quality checked. Transcripts and notes will be subjected to rigorous thematic analysis [62]. Results from the qualitative analysis of process evaluation data will be integrated with results from quantitative statistical analysis to address the three study objectives. Overall, the results of this pilot study will inform the design of a future definitive RCT.

#### Objective 1: Piloting the intervention

Acceptability of the intervention will be assessed by statistically exploring compliance patterns. This will involve the calculation of patterns of adherence, i.e., attendance rates, completion rates, and proportion of homework completed. Descriptive statistics will be used to evaluate whether levels of adherence and variability in adherence depend on therapy group and basic participant characteristics, such as gender, age, and symptom severity. Rate of loss to follow-up and its dependence on adherence level and on basic participant characteristics will be explored. The quantitative results will be combined with results from the qualitative process evaluation to suggest recommendations for specific adaptations to the intervention components and delivery. Qualitative and quantitative measures will be used to investigate whether the processes and changes subjectively experienced by participants correspond with the processes outlined in the WELLFOCUS model.

#### Objective 2: Piloting the trial processes

Descriptive statistics will be used to assess recruitment rates in relation to referrals received by clinical staff. Mean time between referral and consent will be calculated. Attrition between referral, consent, and randomisation will be described. Waiting times will be analysed in relation to attrition rates. The proportion of those receiving the intervention as allocated will be calculated. Those receiving and not receiving the intervention will be compared on participant characteristics. Qualitative data will supplement quantitative data to explain discrepancies between allocation and receipt of intervention. Reasons for facilitator drop-out will be explored in the qualitative analysis. Qualitative data from clinician feedback and quantitative data on recruitment rates will be used to formulate recommendations for adapting recruitment procedures, eligibility criteria, participant information, and seeking consent. Any issues arising with regards to randomisation procedures from the qualitative process evaluation and researcher feedback will be used to suggest improvements. Feedback from researchers and participants will be used to suggest improvements to the feasibility of data collection forms.

#### Objective 3: Piloting the evaluation strategy

The usefulness of fidelity and process evaluation approaches will be determined by exploring whether researcher ratings of fidelity to the manual and process factors, such as engagement and beneficial effect of exercises, helps to improve prediction of outcome and future attendance as compared to recording group attendance only. The confidence interval approach will be used to help determine the suitability of the outcome measures and to inform the sample size calculation for a definitive RCT. This approach involves estimating the confidence interval of the difference between intervention and control group at follow-up, adjusted for baseline. The inclusion of zero (i.e., point of no effect) and the inclusion of a clinically relevant effect into the confidence interval will help to estimate the suitability of measures for a definitive RCT [28]. Further considerations to be taken into account for the choice of outcome measure for the definitive RCT will include the acceptability of the scale (as measured by the number of missing responses), the magnitude of correlation between baseline and follow-up on this scale, and the overall variance of the scale. The group means, standard deviations, and correlations between baseline and follow-up will be used to inform the sample size calculation for the definitive RCT.

In addition, outcomes will be analysed to estimate effectiveness of the intervention. This analysis will be done on an intention-to-treat basis, with participants analysed in the group to which they were randomised irrespective of their compliance with the assigned trial arm. To estimate effectiveness of the intervention, WEMWBS (primary outcome) at pre-treatment (baseline) and 3-month follow-up will be analysed using a random effects regression of outcome on trial arm adjusted for baseline score including a random effect to allow for between group variations in the intervention arm. Where relevant, we will also consider using other approaches to address missing data such as complier-average causal effect approaches [63].

Divergence of normality will be assessed for the distribution of all variables as will linearity of correlations and equality of variance. The choice of statistical methods will be adapted accordingly. *P* values of 0.05 will be considered significant in all cases. All analyses will be carried out in SPSS Version 20 and Stata Version 12.

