### Study setting

Patients are recruited from seven teams and two research registers across the South London and Maudsley NHS Foundation Trust (SLaM). SLaM employs 4,500 staff in 296 teams, works with 34,128 service users, and provides adult mental health services across four Boroughs (Croydon, Lambeth, Lewisham, and Southwark). These services are provided through Clinical Academic Groups organised according to diagnoses; these groups bring together clinical services, research, education, and training for the benefit of patient care. This study takes place in the SLaM Psychosis Clinical Academic Group.

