### Sample size

A sample size of n = 30 per arm has been recommended for pilot studies to estimate location (mean) and variability (standard deviation) of candidate outcome measures to inform later sample size calculation [28]. WELLFOCUS PPT is conducted as a group intervention with about 8 participants in each group. We aim to conduct five waves of PPT groups versus control, each starting with 16 participants (n = 8 in the intervention and n = 8 in the control arm), giving a total sample of 80. Allowing for a drop-out rate of 20%, consistent with attrition in a feasibility study of a similar intervention with service users with psychosis [9], this gives an analysable sample of n = 32 per arm to generate estimates for well-being as our primary outcome. However, we will try to minimize dropouts in our study as suggested by Little et al. [31].

The Warwick-Edinburgh Mental Well-being Scale (WEMWBS) was shown to have a one-week re-test reliability of 0.83 [32]. The correlation between baseline and 3-months follow-up can be assumed to be below that. Assuming a correlation of 0.7 the power to detect an effect size of 0.5 on the WEMWBS at follow-up, adjusted for baseline, would be at 0.80. A more conservative estimate of a correlation between baseline and follow-up of 0.6 would allow us to detect the same effect size with a power of 0.71. Higher effect sizes would provide higher power. For example, an effect size of 0.6 could be detected with a power of 0.85 assuming a correlation between baseline and follow-up of 0.6. All power calculations are based on a significance level of 0.05 and were calculated using the STATA 12.

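### Randomisation is by team/wave batch, but the primary model has no batch term; if batches differ beyond baseline, the confidence interval is too wide and the therapy-group variance is inflated

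*Protocol article*

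**What the plan says.** **Randomisation.** The section Recruitment and randomisation says: "When participants from a participating clinical team have all been entered into the database, randomisation is conducted". It adds: "Randomisation involves independent allocation to one of the two trial arms on a 1:1 basis". Blocks are used, and the smallest batch is given as 8 participants, 4 per arm. The same section says: "The use of stratification was considered disproportionate for a pilot RCT".

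**Waves.** The Sample size section says: "We aim to conduct five waves of PPT groups versus control, each starting with 16 participants", split 8 and 8. After 20% drop-out, "this gives an analysable sample of n = 32 per arm".

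**Sources.** Under Study setting: "Patients are recruited from seven teams and two research registers".

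**Primary model.** The Analysis plan, Objective 3, writes out a random effects regression of WEMWBS on trial arm, "adjusted for baseline score including a random effect to allow for between group variations in the intervention arm". It names no team, wave or batch term.

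**Use of the interval.** Objective 3 also uses the baseline-adjusted confidence interval for the arm difference to judge which outcome measures suit a definitive trial. The criteria are whether the interval contains zero and whether it contains a clinically relevant effect.

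**The concern.** Each batch is split evenly between the arms, so it acts as a stratum although none is declared. The therapy group is essentially the intervention half of a batch, and the other half are its concurrent controls. Anything that raises or lowers follow-up scores in both halves (team, site, season) drops out of the arm contrast.

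The stated model cannot represent such a shared effect. In the intervention arm it can only enter the therapy-group random effect. In the control arm, members of the same batch are treated as independent. The model therefore charges the arm comparison with variation that the design has already removed.

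At stake are the width of the primary confidence interval and, if the Objective 3 intervals come from the same model, the judgement on outcome measures. The estimated therapy-group variance would also include differences between teams.

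**Working it through.** **Inputs from the article.** n = 32 analysed per arm; k = 5 waves; effect size d = 0.5; baseline to follow-up correlation r = 0.7; significance level 0.05, taken as two-sided.

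**Assumed, because the documents give no figure.** Batch variance t in follow-up WEMWBS, unrelated to baseline, on a scale where the total variance without it is 1. True therapy-group variance is set to 0.

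**1. The plan's own figure.** Residual variance after baseline is e = 1 − 0.7² = 0.51. SE = √(2 × 0.51/32) = √0.031875 = 0.1785. Power = Φ(0.5/0.1785 − 1.96) = 0.80, as stated. The same formula gives 0.71 for d = 0.5, r = 0.6 and 0.85 for d = 0.6, r = 0.6, also as stated.

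**2. Closed form with batch variance.**
- True variance of the arm effect: 2e/n. The batch effect cancels.
- Variance implied by the stated model: e/n + t/k for the intervention arm, plus (e + t)/n for the control arm.
- Type I error = 2[1 − Φ(1.96 × model SE/true SE)]; power = Φ((0.5 − 1.96 × model SE)/true SE).

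| t | t/(t + e) | model variance | model SE | true SE | ratio | type I error | power |
|---|---|---|---|---|---|---|---|
| 0 | 0 | 0.0319 | 0.179 | 0.179 | 1.00 | 0.050 | 0.80 |
| 0.05 | 0.09 | 0.01594 + 0.01 + 0.0175 = 0.0434 | 0.208 | 0.179 | 1.17 | 0.022 | 0.70 |
| 0.10 | 0.16 | 0.01594 + 0.02 + 0.01906 = 0.0550 | 0.235 | 0.179 | 1.31 | 0.010 | 0.59 |

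The second column is also the therapy-group ICC that the stated model would show on average where the true value is 0.

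**3. Simulation of the same case** (REML, 5 waves of 16, 20% drop-out, 1,200 trials per scenario).
- t = 0.05: mean model SE 0.215 against a true 0.185, ratio 1.16; type I error 0.037; power 0.65, or 0.69 with fixed wave terms; mean ICC 0.09.
- t = 0.10: mean model SE 0.237 against 0.181, ratio 1.31; type I error 0.026; power 0.59, or 0.71 with fixed wave terms; mean ICC 0.135.
- With fixed wave terms the mean ICC is still about 0.07, although the truth is 0.

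Not all of the simulated excess comes from batches. In a separate simulation of 1,500 trials with no batch variance, the stated model already averaged an SE of 0.189 against an empirical 0.176, and an ICC of 0.038. A variance component cannot be estimated below zero.

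**4. The opposite case: a stable team effect present at both visits.** With a baseline slope of about 0.7, adjustment leaves (1 − 0.7)² = 0.09 of its variance. A team share of 5% leaves 0.05 × 0.09 = 0.0045; 10% leaves 0.009. With e held at 0.51, the closed form gives SE ratios of √(0.03292/0.031875) = 1.02 and √(0.03396/0.031875) = 1.03. Simulation agrees. At a 5% share the stated model has SE 0.185 (empirical 0.179) and power 0.79; fixed wave terms give SE 0.194 and power 0.76.

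**5. Form of the extra term.** With no batch variation, a batch random intercept common to both arms gave simulated power of 0.78 against 0.77 for the stated model. At t = 0.10 it gave 0.74 against 0.61. Fixed wave terms with no batch variation cost 3 to 5 points (0.756 to 0.723 in one simulation, 0.765 to 0.722 in another).

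**The case against.** The strongest reply is that the loss depends on batch effects unrelated to baseline. Team case-mix would normally show in baseline WEMWBS, which the model already adjusts for, and then the stated model does as well as or slightly better than one with fixed wave terms. This stands. It is why the size is conditional and why fixed terms are not the preferred remedy.

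Second, seven teams and two registers need not map one-to-one onto five waves, so batch and therapy group may coincide only in part. This also stands, and the term should be the batch actually randomised.

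Third, an analysis plan might add the term. That would settle the matter, but the article writes its model out, and the model as written omits it.

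Three stronger readings are tempting and are not supported:
- That the standard errors are wrong whatever happens. They are wrong only if batches differ after baseline adjustment.
- That the trial risks false positives or a biased effect. The error is conservative and the arm estimate is unbiased. The Hypotheses section also says that testing is not the main objective.
- That an ICC promised for the definitive trial is spoiled. Objective 3 carries forward means, standard deviations and correlations and names no ICC. From about five groups an ICC is poor under any of these models.

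**Conclusion.** The point holds conditionally. The analysis does not reflect the batches within which the trial randomises. Batch variation left after baseline adjustment is read as therapy-group variance, so the interval is too wide, power is lost and the group variance is inflated.

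The SE is roughly 15–30% too large if batch variance unrelated to baseline is 5–10% of total variance. The excess is negligible if team differences are stable and already visible at baseline. Both cases are assumptions. These figures also assume five equal batches, each matching one therapy group, no true therapy-group effect and r = 0.7.

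The consequence for Objective 3 depends on its intervals coming from this model, which the article does not state outright. If they do, an over-wide interval is more likely to contain both zero and a clinically relevant effect, and so says less about each measure.

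**What to change.** Add the actual randomisation batch to the primary model as a random intercept common to both arms, and keep the intervention-arm therapy-group random effect. Use the same model for the secondary outcomes and for the baseline-adjusted intervals under Objective 3. If any therapy-group variance is reported, say that about five groups estimate it imprecisely and that it is biased upwards when the true value is near zero.

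The cost is one variance component. Randomising by batch already generates the variable, and in simulation the random intercept cost no power when batches did not differ. Fixed batch terms are an acceptable alternative but cost about 3–5 points of power in that case.
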